#### Statistical analysis plan

As per the predetermined statistical analysis plan, the baseline characteristics of participants will be summarised separately for the two IST models. Categorical variables will be reported as counts and percentages, while continuous variables will be summarised as means and SDs or medians and IQRs as appropriate depending on the distribution of the data.

The primary outcome is challenging behaviour measured by total score on the ABC. Change in ABC total score from baseline to 9-month follow-up will be calculated for each participant. The mean difference in ABC score between the two IST models will be estimated from a multilevel linear regression model with change in ABC score as the outcome, a fixed effect of model as the main exposure, and a random effect of IST to account for clustering within services.

Age, gender, living arrangements, level of ID, level of risk, presence of autism and clinical comorbidities have been identified as potential confounders and will be specified as covariates in adjusted multilevel linear regression models similar to the main unadjusted model described above. The estimated difference in change in ABC total score from both unadjusted and adjusted models will be reported with accompanying 95% CI and p value.

The secondary outcomes detailed above will be analysed using statistical models analogous to those for the primary outcome. Binary outcomes will be analysed using multilevel logistic regression models. Non-normally distributed continuous outcomes will be analysed using the bootstrap method and bias corrected 95% CI will be reported. P values will not be reported for secondary outcomes.

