**Trial registration number:**

ClinicalTrials.gov Registry (NCT03586375).

Strengths and limitations of this studyThis study will be the first systematic national evaluation of intensive support team (IST) models for adults with intellectual disability who display challenging behaviour.Accessing the experience of stakeholders (eg, IST managers, staff members, family and paid carers, and service users) will enable an in-depth understanding of how ISTs function and how they respond to people with complex needs.This is not a randomised controlled trial so may be subject to biases associated with observational research.

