### Setting and participants

Eight enhanced service provision ISTs and eight independent service provision ISTs (table 1) will be selected at random from ISTs surveyed in phase 1 of the study.^20^ Service users, either already under the care of the 16 ISTs or newly referred, and their caregivers will be identified by IST staff either at first clinical assessment or from the IST services caseloads and asked if they are interested in taking part in the study. Following an expression of interest, the researchers will contact them to provide information about the study and to obtain written or audio-recorded informed consent from those agreeing to undergo further research assessments.

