#### Economic evaluation plan

As per the predetermined health economic analysis plan, we shall derive and report the costs of each IST service model over 9 months. To calculate the cost of each IST service model, we will use information on the description, time inputs of staff and related caseloads of professionals in the IST.

The cost-effectiveness analyses will be conducted from a health and social care perspective and a wider societal perspective. Data on health and social care services and support provided by statutory services external to the ISTs will be obtained from the CSRI covering a retrospective period of 6 months. To service use and support data, we shall attach unit costs taken from a wide range of sources.^30 31^ Costs of unpaid care will be estimated from information on volume and type of support, the opportunity cost of lost work (wage rate) for carers in paid employment and replacement cost for those not in paid employment based on cost of a home care worker. We shall extrapolate the 6-month costs over the 9-month period and examine the link between costs and sociodemographic, clinical characteristics of individuals in the study.

The cost-effectiveness of one IST model over another will be compared by calculating incremental cost-effectiveness ratios, defined as difference in mean costs divided by difference in mean effects. Cost-effectiveness acceptability curves^32^ will be plotted for each cost–outcome combination to show the likelihood of one IST model as cost-effective relative to another for a range of (implicit) values placed on incremental outcome improvements. Using the net benefit (NB) approach, monetary values of incremental effects and incremental costs are combined, and NB derived as: NB=λ×(effect_b_−effect_a_)−(cost_b_−cost_a_). Where, λ is the willingness to pay for a unit improvement in effectiveness (ABC, QALYs and QoL) and subscripts ‘a’ and ‘b’ denote *IST model a* and *IST model b*, respectively. This approach allows costs and outcomes to be considered on the same monetary scale, taking account of sampling uncertainty and adjusting for baseline covariates and clustering.

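### In a comparison that is not randomised, the plan labels the covariate-free model as the main one and gives unadjusted and adjusted results a p value each, without saying which carries the conclusion

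*Protocol article*

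**What the plan says.** The strengths and limitations box of the Protocol article concedes: "This is not a randomised controlled trial so may be subject to biases associated with observational research". Under Setting and participants, the random element is the choice of teams within each model: "Eight enhanced service provision ISTs and eight independent service provision ISTs (table 1) will be selected at random from ISTs surveyed in phase 1". Nobody is allocated to a model.

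Under Statistical analysis plan, the primary outcome is change in ABC-C total score from baseline to 9 months. The first model described has "a fixed effect of model as the main exposure, and a random effect of IST to account for clustering within services", and no covariates. The section then states: "Age, gender, living arrangements, level of ID, level of risk, presence of autism and clinical comorbidities have been identified as potential confounders". These factors are to enter "adjusted multilevel linear regression models similar to the main unadjusted model described above". The estimated differences "from both unadjusted and adjusted models will be reported with accompanying 95% CI and p value". For the other endpoints, "P values will not be reported for secondary outcomes".

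The Economic evaluation plan, which lists ABC among its effects, describes its net-benefit approach as "taking account of sampling uncertainty and adjusting for baseline covariates and clustering".

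**The concern.** The first specific objective is to find which service model gives better outcomes, and the findings are meant to inform commissioning. With no randomisation, a plain contrast between models mixes any effect of the model with any difference in the people each model serves. The authors recognise this by listing seven factors, yet the word that ranks the analyses is attached to the one that leaves all seven out.

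Table 1 gives a reason to take the issue seriously. The models differ in referral route (self-referral accepted versus referral through professionals), in length of support and in caseload. Those are routes by which case mix could differ for reasons unrelated to effectiveness.

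Two things are at stake. The result presented as the main answer could be the one more exposed to bias. And if the unadjusted and adjusted results fall on opposite sides of 5%, the article does not say which one answers the question.

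**Working it through.** **1. The statements side by side**

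- Design: not randomised, by the article's own account.
- Model labelled as main: IST model plus a random effect of team, no covariates.
- Confounders named: seven, used only in further models (the article uses the plural).
- P values on the primary outcome: at least two. On secondary outcomes: none.
- Economic comparison: adjusted for baseline covariates.

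The label is a stated choice, and it sits badly with the first and last items.

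**2. The plan's own sample size**

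Inputs from Sample size: 0.45 SD, 5% significance (taken as two-sided), 80% power, intraclass correlation 0.02, 15% loss. From Setting and participants: 8 teams per model, so 96/8 = 12 participants per team.

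- Unclustered n per model = 2 × ((1.960 + 0.842)/0.45)² = 77.5, rounded up to 78.
- Design effect = 1 + (12 − 1) × 0.02 = 1.22.
- 78 × 1.22 = 95.2, rounded up to 96, as stated.
- 96/(1 − 0.15) = 112.9, rounded up to 113, as stated.

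The sample size is not in dispute. It contains no covariate term.

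**3. What a bias would do to the unadjusted test**

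The article gives no figure for confounding, so the bias b is an assumption, in SDs of the analysed outcome. With the planned numbers, SE = √(2 × 1.22/96) = 0.159 SD. If the models truly do not differ, the chance that the unadjusted test rejects is 1 − [Φ(1.96 − b/SE) − Φ(−1.96 − b/SE)].

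| Assumed b (SD) | b as share of 0.45 SD | b/SE | False-positive rate |
|---|---|---|---|
| 0 | 0% | 0 | 5.0% |
| 0.05 | 11% | 0.31 | 6.1% |
| 0.10 | 22% | 0.63 | 9.6% |
| 0.15 | 33% | 0.94 | 15.6% |
| 0.20 | 44% | 1.25 | 24.1% |

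For orientation, a binary factor that shifts change in ABC-C by 0.3 SD and is 20 percentage points more common in one model gives b = 0.3 × 0.20 = 0.06 SD (6.6% error). A factor worth 0.5 SD with the same gap gives 0.10 SD (9.6%). The second is a strong assumption, since 0.5 SD exceeds the study's own target difference.

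**4. What two p values would do**

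This matters only if either p value may support the claim. The probability that at least one of two two-sided 5% tests rejects under the null, from the bivariate normal distribution, is 8.3% at correlation 0.7, 7.8% at 0.8, 7.0% at 0.9 and 6.5% at 0.95. The figure for independent tests is 1 − 0.95² = 9.75%. The correlation is assumed. Unadjusted and adjusted tests on the same participants will usually be strongly correlated, so the lower figures are the more plausible ones.

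**The case against.** The strongest reply is that the adjusted analysis is already prespecified and will be reported with its interval and p value beside the unadjusted one. The listed factors are therefore not ignored, and readers will see both results. This stands, and it narrows the point to designation.

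Second, the word main may merely point back to the model structure just described. And if it is a ranking, there is a rule and the two tests do not compete; if it is not, a rule may lie in the separate analysis plan, which is not shown. This partly stands. The missing rule alone would be a weak point. The label is printed, however, and on its natural reading it ranks the unadjusted model first.

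Third, a reader might infer that the main contrast is confounded, or that participants in the two models differ in housing or severity of disability. The documents do not show this. Table 1 supports a difference in referral route; living arrangements and level of ID are listed only as potential confounders. The outcome is also a change score, which removes stable differences in ABC-C level, so a factor must predict change to bias the contrast. The most that can be said is that the contrast is open to confounding.

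Fourth, adjustment is not free of risk here. Participants may join at any point of IST care, so risk and comorbidity recorded at baseline may already reflect exposure to the model. This stands as a caution about the fix. It does not justify preferring an estimate with no control at all.

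**Conclusion.** The point holds as one of designation: a comparison acknowledged to be observational gives its main label to the model without confounder control, although an adjusted model is already planned and the economic comparison is adjusted.

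The greater risk is bias in the estimate so labelled. Its size and direction are unknown; the range of about 6% to 24% rests on assumed shifts of 0.05 to 0.20 SD, the planned 96 per model, a design effect of 1.22 and normal approximations. The either-test error of about 7% to 8% is secondary and depends on a decision rule that the article never states. A reader might take it as the trial's actual error rate, but the text does not support that. Nor would adjustment for the seven factors remove unmeasured confounding.

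**What to change.** State that the primary analysis is one multilevel linear model of change in ABC-C total score with IST model, a random effect of IST and all seven named confounders together, and that its p value alone carries the conclusion. Report the unadjusted estimate with its 95% CI as descriptive, without a decision-bearing p value.

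Costs and cautions:

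- The sample size statement need not change.
- A rule is needed for missing covariates; otherwise those participants drop out of the primary model.
- The text should acknowledge that risk and comorbidity may already reflect earlier IST care in people recruited mid-care. A sensitivity analysis leaving those two out would show whether this matters.
- Study progress and COVID-19 impact reports that recruitment has closed and 180 follow-ups are complete. The change should be dated, justified and documented before the analysis is run.

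Baseline ABC-C is not on the article's covariate list. Adding it is a separate decision, because change-score and baseline-adjusted analyses can answer different questions when groups are not randomised. It is best treated as a sensitivity analysis.

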#### Economic evaluation plan

As per the predetermined health economic analysis plan, we shall derive and report the costs of each IST service model over 9 months. To calculate the cost of each IST service model, we will use information on the description, time inputs of staff and related caseloads of professionals in the IST.

The cost-effectiveness analyses will be conducted from a health and social care perspective and a wider societal perspective. Data on health and social care services and support provided by statutory services external to the ISTs will be obtained from the CSRI covering a retrospective period of 6 months. To service use and support data, we shall attach unit costs taken from a wide range of sources.^30 31^ Costs of unpaid care will be estimated from information on volume and type of support, the opportunity cost of lost work (wage rate) for carers in paid employment and replacement cost for those not in paid employment based on cost of a home care worker. We shall extrapolate the 6-month costs over the 9-month period and examine the link between costs and sociodemographic, clinical characteristics of individuals in the study.

The cost-effectiveness of one IST model over another will be compared by calculating incremental cost-effectiveness ratios, defined as difference in mean costs divided by difference in mean effects. Cost-effectiveness acceptability curves^32^ will be plotted for each cost–outcome combination to show the likelihood of one IST model as cost-effective relative to another for a range of (implicit) values placed on incremental outcome improvements. Using the net benefit (NB) approach, monetary values of incremental effects and incremental costs are combined, and NB derived as: NB=λ×(effect_b_−effect_a_)−(cost_b_−cost_a_). Where, λ is the willingness to pay for a unit improvement in effectiveness (ABC, QALYs and QoL) and subscripts ‘a’ and ‘b’ denote *IST model a* and *IST model b*, respectively. This approach allows costs and outcomes to be considered on the same monetary scale, taking account of sampling uncertainty and adjusting for baseline covariates and clustering.

#### Qualitative analysis plan

Interviews will be audio-recorded and transcribed verbatim by an external agency. Data will be analysed using thematic analysis^33^ conducted using NVivo software. A staged, collaborative and primarily inductive analytical approach will be adopted, allowing us to iteratively develop a set of themes to capture key concerns and topics, as well as more abstract or underlying issues. Although numbers in stakeholder groups linked to each IST model may be relatively small, triangulation of the various stakeholder perspectives will allow us to obtain a broad picture of each IST model. Thus, we will be able to compare the IST models in terms of multiple stakeholders’ views, as well as analysing the data set as a whole to understand broadly common views and experiences of ISTs. Analysis will involve close collaboration between study researchers, the qualitative lead and other key members of the study team. Service user and carer group meetings will be scheduled three times per year. The members of the advisory groups will receive easy read summary documents to be informed about the study progress, share views on different recruitment strategies, comment on the coding, analysis and interpretation of study findings.

### Patient and public involvement

A service user reference group (Camden Disability Action) has supported the project and assisted with the research governance requirements including input to easy read versions of study materials (ie, information sheets, consent forms) and piloting of instruments and qualitative interview topic guides with reference to people with ID. Family carer representatives from the Challenging Behaviour Foundation, an independent national charity of family carers of people with IDs and challenging behaviour, have also been involved in the conduct of the study and advising on recruitment as well as reviewing study-related information including the qualitative interviews topic guides. Meetings with both expert by experience groups are scheduled to take place every 3 months. Finally, there is service user and family caregiver representation at the study Steering Committee overseeing the study.

## Ethics

Ethical approval for this study was granted on 26 June 2018 by the London Bromley Research Ethics Committee (REC) (18/LO/0890). All personal data are handled in accordance with the Data Protection Act. All outcome measures are stored electronically, and access is restricted to the principal investigator of the study and nominated researchers. All identifiable documents are saved as password-protected files on password-protected computers. Confidential information (including signed consent forms) are stored separately from paper records (eg, Clinical Research Forms) in locked filing cabinets in a restricted area accessed by members of the University College London, Division of Psychiatry. Data management and data quality checks will be performed by the research study team.

### Dissemination plan

Our dissemination plan was developed in close collaboration with PPI representatives. Our dissemination and impact activities will include open-access academic publications in high-impact journals, presentations at academic and non-academic conferences, hosting a free public webinar about the study and producing briefings for carer groups, charities and NHS services. A newsletter about the study progress will be sent to participants every 6 months and also available on the study website (https://www.ucl.ac.uk/psychiatry/research/epidemiology/pis/[name]-research-portfolio/intensive-support-teams). The research team will submit manuscripts to peer-reviewed publications, and authorship inclusion and order will be guided by levels of contribution. All publication material will acknowledge the funding contribution from the National Institute for Health Research. Requests for access to the anonymised data and statistical code should be addressed to the corresponding author once the study funder report and main papers are published.

### Study progress and COVID-19 impact

The first phase of the study has been completed and reported.^20^ The study has faced recruitment challenges which in the main included: reduced capacity to identify sufficient numbers of eligible participants due to small and static caseloads, services withdrawing or changing their remit halfway through the study, inadequate communication between ISTs and Clinical Research Networks which hampered research support. The number of ISTs was expanded to 23, 21 of which contributed participants to the study. The originally estimated 9 months of recruitment were extended to 17 with the last participant enrolled in May 2020; 180 9-month follow-ups have been completed. The last 4 months of recruitment occurred during the coronavirus pandemic and the subsequent lockdown which necessitated changes in study procedures including the introduction of remote completion of the research assessments and qualitative interviews. Those changes were non-substantial amendments (number 7) to the REC that had originally approved the study. Thirteen participants have been lost to follow-up with one death from COVID-19.

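### Under even accrual about three quarters of 9-month ABC-C endpoints fall in the pandemic, yet the adjusted models carry no term for calendar period

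*Protocol article*

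**What the plan says.** On timing, the section on study progress and COVID-19 impact states: "The originally estimated 9 months of recruitment were extended to 17 with the last participant enrolled in May 2020". It adds that "The last 4 months of recruitment occurred during the coronavirus pandemic and the subsequent lockdown", and that this led to "changes in study procedures including the introduction of remote completion of the research assessments and qualitative interviews". It also reports that the number of ISTs grew to 23, of which 21 contributed participants, and that some services withdrew or changed remit during the study. The section on setting and participants had planned 16. When the article was written, "180 9-month follow-ups have been completed".

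On the analysis, the statistical analysis plan section says: "Change in ABC total score from baseline to 9-month follow-up will be calculated for each participant". The main model has IST model as a fixed effect and IST as a random effect. For the adjusted models, "Age, gender, living arrangements, level of ID, level of risk, presence of autism and clinical comorbidities have been identified as potential confounders". Secondary outcomes use analogous models. Neither calendar period nor mode of assessment is named, and the section on the pandemic links it to no change in the analysis.

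**The concern.** The outcome is a change score, and for many participants the 9-month interval spans the start of the pandemic. Lockdown could plausibly alter behaviour, carer contact, service use and admissions, and the way some assessments were completed changed in the same period.

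In a randomised comparison, calendar time would be balanced in expectation. Here it is not. The exposure is a property of the service, only 21 services contributed, and the set of services changed during recruitment. If one model's services enrolled later than the other's, more of its change scores would straddle the onset, and part of any period effect would be read as an effect of IST model. The random effect of IST allows for clustering. It does not remove confounding between models. Even with balanced calendars, an unmodelled period effect adds residual variance that could be avoided.

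**Working it through.** **Inputs from the article.** Recruitment R = 17 months; pandemic part of recruitment P = last 4 months; follow-up F = 9 months; target difference 0.45 SD; planned sample 96 per model evaluable, 113 per model recruited.

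**The plan's own figure.** The article gives no share of endpoints in the pandemic. Its sample size does reproduce, so 0.45 SD is a fair yardstick. Two means at 0.45 SD, 5% two-sided (assumed) and 80% power need 78 per arm. With 96/8 = 12 per IST the design effect is 1 + (12 − 1) × 0.02 = 1.22, and 78 × 1.22 = 95.2, rounded up to 96. Then 96/0.85 = 112.9, rounded up to 113.

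**Share by period, even accrual (assumed).** Let t be the month of enrolment. The onset is at 17 − 4 = 13, follow-up is at t + 9, and the pandemic period is taken to last to the final follow-up (assumed).

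- Both assessments before: t < 4, so 4/17 = 23.5%.
- Straddling: 4 ≤ t < 13, so 9/17 = 52.9%.
- Both within: t ≥ 13, so 4/17 = 23.5%.
- Endpoint in the pandemic: (P + F)/R = 13/17 = 76.5%.

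**Sensitivity to accrual (assumed patterns), endpoint in the pandemic.**

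| Pattern | Formula | Share |
|---|---|---|
| Linearly falling | (13/17)² | 58% |
| Linearly rising | 1 − (4/17)² | 94% |
| First 4 months at half the later rate | 13/(13 + 4 × 0.5) | 87% |
| First 4 months at twice the later rate | 13/(13 + 4 × 2) | 62% |
| First 4 months at three times the later rate | 13/(13 + 4 × 3) | 52% |
| Only 2 recruitment months count as pandemic, even accrual | (2 + 9)/17 | 65% |
| Only 3 recruitment months count as pandemic, even accrual | (3 + 9)/17 | 71% |

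The share is a majority in every pattern. The straddling share is 52.9% under both linear patterns as well, since (13² − 4²)/17² = 153/289.

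**Size of a possible bias (both inputs assumed).** If straddling the onset shifts ABC-C change by s SD, and the straddling share differs between models by d, the unadjusted contrast moves by s × d.

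| s (SD) | d | Bias (SD) | Share of 0.45 SD |
|---|---|---|---|
| 0.3 | 0.20 | 0.06 | 13% |
| 0.3 | 0.30 | 0.09 | 20% |
| 0.5 | 0.20 | 0.10 | 22% |
| 0.5 | 0.30 | 0.15 | 33% |
| any | 0 | 0 | 0% |

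The last row assumes that the period effect is the same in both models.

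**The case against.** The strongest objection is that the article summarises a predetermined analysis plan that is not shown, and that handling of the pandemic is commonly left to such a plan or its amendment. This stands in part: the full plan may already contain a period analysis. But the article does more than stay silent. It names the adjustment set, and it does so in a text written after the pandemic's effect on the study was known. A stated covariate list for a non-randomised comparison can be judged as stated.

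Second, no bias is shown. A reader might infer from the 76% that the model contrast is distorted. The article does not support that. A shift common to both models cancels. Bias needs calendars that differ between models, or a pandemic effect that differs by model. The article does not say when services were added or withdrew, or which model they belonged to. Variation in enrolment time between services is a plausible inference, and it is still not imbalance between models. This objection stands in full.

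Third, a reader might take it that assessment switched to remote and that mode therefore belongs in the adjusted model. The article reports only the "introduction of remote completion of the research assessments and qualitative interviews", not that all assessments became remote. It does not say that mode was recorded for each assessment. Mode would also be nearly collinear with period, mode at follow-up is fixed after exposure, and the ABC-C is a checklist completed by a caregiver, for which a large mode effect is not self-evident. This also stands, and it limits mode to a sensitivity analysis.

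**Conclusion.** The point holds as a cheap and worthwhile improvement to a stated adjustment set. It does not demonstrate bias. On the article's 17, 4 and 9 months, about 76% of primary endpoints fall in the pandemic and about 53% of change scores straddle its onset. Both figures assume even accrual, which the article does not report, but the 76% remains a majority (52% to 94%) under every pattern tried. The named confounders have no term for this.

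The figures of 0.06 to 0.15 SD (13% to 33% of the target difference) are illustrations from assumed inputs and should not be read as estimates. They are zero if the two models enrolled on the same calendar and the pandemic affected both alike. What the article does support is that nothing in the design ensures balanced calendars: the comparison is observational, exposure is set at service level, 21 services contributed, and the set of services changed during recruitment.

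**What to change.** - Add a three-level pandemic-period term to the adjusted primary and secondary models: both assessments before, straddling, or both within. Set it from assessment dates against one onset date, fixed before the models are compared.
- Tabulate period by IST model, so that readers can see whether the calendars differ.
- Use assessment mode, where recorded, in a sensitivity analysis only.
- If the full analysis plan already contains a period analysis, state it in the article's analysis section.

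The cost is a change of wording and about two degrees of freedom, against 192 planned evaluable participants. No new data are needed for the period term, because it follows from enrolment and assessment dates. Period is set by the calendar and is not a consequence of IST model, so adjusting for it does not remove part of the effect of interest. A main-effect term deals with imbalance in timing. It would not correct for a pandemic effect that differs between the models, and that limit should be stated when the results are interpreted.
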